## Discussion

The main aims of the Vold-study are to assess the effects of a self-composed vegan diet in comparison to an omnivorous diet on thigh muscle volume in healthy, community-dwelling, older individuals, and to investigate whether RE may attenuate any potential reductions in muscle volume while consuming a vegan diet. To our knowledge, this is the first trial to assess the health effects of a longer term self-composed vegan diet in older adults. The high environmental impact of animal-based food production and health benefits related to the increased consumption of plant-based foods have led to the adoption of more plant-centered dietary guidelines [1–3], and the increased implementation of plant-based meals and diets by consumers and healthcare institutions [47–49]. However, the consequences of longer term adherence to a self-composed fully plant-based, i.e. vegan, diet for skeletal muscle and other health outcomes in older individuals remain unknown.

Previous studies have assessed the acute effects of the consumption of plant-based protein isolates [20, 50, 51], a vegan meal [26] and a vegan diet [23, 24] on MPS in older individuals in highly controlled settings. Monteyne et al. [24] observed no difference in MPS rates during a three day controlled mycoprotein based vegan diet with a high protein content in comparison to an isonitrogenous omnivorous diet. Additionally, we recently observed no differences in MPS between a highly controlled vegan and omnivorous diet with ample protein in older adults as well [23]. Nevertheless, we expect that a self-composed, longer term, vegan diet will differently impact skeletal muscle in our older participants during the 12-week intervention period. Although highly controlled dietary intervention studies are essential in assessing the inherent differences between specific components of a food product or diet, longer term adherence to a self-composed diet will result in the consumption of different food products, and hence nutrients. The framework of our intervention was therefore specifically chosen to allow for a higher external, especially ecological, validity of the results that will be obtained [52].

The potentially lower anabolic properties of a vegan diet poses a risk for the skeletal muscle health of older individuals, while a vegan diet may concurrently improve risk factors of other age-related non-communicable diseases, as cardiometabolic risk factors [4–6]. By assessing the effects of the intervention on a wide range of other health outcomes as well (Table 1), we anticipate that the results of the Vold-study will provide an extensive overview regarding the consequences of shifting to a vegan diet at an older age, considering both the potential risks and benefits of such a shift. Additionally, although no major nutrient insufficiencies are expected to transpire due to the relatively short duration of the intervention, assessing the status of vitamin D, methylmalonic acid, ferritin and haemoglobin at baseline and at the end of the intervention will provide valuable insights into the risk of development of insufficiencies of cobalamin, vitamin D and iron while consuming a vegan diet later in life. The Vold-study is the first trial to assess the effects of a self-composed vegan diet later in life on such an extensive range of health outcomes. The results will therefore contribute to the substantiation of the envisaged more plant-based dietary guidelines [3, 53].

Given the extent and complexity of the presently proposed study, several challenges and potential limitations will have to be considered. First, the high number of measurements, complexity of the intervention, and the duration of the trial may complicate the recruitment of ample participants. We therefore plan to set out a broad range of recruitment strategies, ranging from (commercial) volunteer databases to advertisements in online and offline media. Second, shifting to a vegan diet is complex and our participants will require adequate guidance. However, as the aim of the Vold-study is to assess the consequences of a *self-composed* vegan diet, it will be essential not to steer participants too much in their dietary choices either. By informing our participants during monthly meetings guided by trained dietitians and by providing practical tools, as pocket-sized hand-outs with (non)vegan ingredients, product logo’s, recipes, product lists, and bi-weekly provision of plant-based food products, we envisage to adequately guide our participants through their shift to a vegan diet, while not imposing our participants with strict rules. Third, we are aware of the possibility that the control group may adopt a more plant-based diet due to increased adherence to the national dietary guidelines and because participants may already have a specific interest in plant-based diets when registering for the Vold-study. We will anticipate on this by providing the participants in the control group with animal-based food products every other week. Additionally, by including participants that habitually consume animal-based food products on at least five days per week and instructing them not to lower their animal-based food intake, we expect no large reductions in animal-based food consumption in the control group. Fourth, maintaining high compliance is a well-known challenge in dietary intervention studies [54]. We aim to keep adherence high by providing self-selected food-products bi-weekly to all participants, both assisting them in adhering to their allocated group as well as allowing us to have bi-weekly contact moments with all our participants. Furthermore, the social aspects of the group meetings, exercise sessions and the possibility of trying new food products will be highlighted throughout the intervention period. Last, participant dropout may result in missing data. To prevent any problems related to participant dropout, we accounted for 20% dropout in our sample size calculation. We further envisage that the aforementioned strategies to improve compliance, will reduce the number of dropouts in the Vold-study. Additionally, participants that withdraw before the initiation of the intervention diets will be replaced. To allow for intention to treat analysis, dropouts will be asked, but not obliged, to visit the research facilities for follow-up measurements.

Although complex, the design of the Vold-study encompasses the important strength of using several gold standard methodologies, as MRI-scanning, the Biodex measurement, and DEXA-scanning for the assessment of muscle volume, fat distribution, muscle strength and bone mineral density, respectively. Magnetic resonance imaging is considered the gold standard in assessing muscle volume as well as fat distribution [55, 56], and its sensitivity will allow us to pick up small changes over the 12-week intervention period. As such, we envisage that we are able to observe the expected changes within the relatively short timeframe of 12-weeks, whereas a longer study duration would have been needed if less a sensitive measurement method was chosen. The same applies for the Biodex measurement, which is a widely used method to accurately assess muscle strength [57, 58]. Using these high standard methods to assess muscle volume, MFI as well as muscle strength, enables us to gain valuable insights in overall change in muscle quality and function in response to the intervention rather than in muscle volume alone. Loss of muscle strength and function are, in addition to muscle mass, strong predictors for adverse health outcomes and are key characteristics in the identification of sarcopenia [59]. Furthermore, additionally assessing the short-term effects on mixed MPS rates, allows us to investigate to what extent the differences between groups in mixed MPS response translate to the longer term differences in muscle volume. Although the effects of RE on myofibrillar MPS rates correlate well with training induced muscle hypertrophy in trained individuals, it remains to be explored to what extent the acute effects of a dietary intervention on mixed MPS rates translate into longer term adaptations in thigh muscle volume [60, 61].

This 12-week randomized controlled trial aims to assess the effects of a self-composed vegan diet, with or without coinciding RE, on muscle related outcomes and a broad range of other health related outcomes in older adults. The findings will fill major gaps in the literature regarding the health consequences of shifting to a vegan diet later in life, and will provide insights regarding the health implications of the envisaged shift towards more plant-based dietary guidelines.

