## Methods and design

### Study design

#### Study overview

This study is an open-label, single-center, randomized controlled trial with three parallel study arms. A general overview of the design is presented in Fig. 1. The study duration for enrolled participants will be approximately 14 weeks. Following inclusion, the participants will be randomized to follow either their habitual omnivorous diet (OMNI), a self-composed vegan diet (VEG), or a self-composed vegan diet with concurrent resistant exercise twice a week (VEG-RE) for 12 weeks. All groups will be guided through monthly nutrition information meetings. Measurements to assess the study outcomes will be performed at baseline, after 10 days, after 6 weeks and after 12 weeks. Additionally, all participants will follow a deuterium oxide protocol during the first ten days of the intervention period to allow for the assessment of mixed MPS rates. A detailed description of all measurements can be found in the subsequent paragraphs. Measurements will take place at the hospital Gelderse Vallei (Ede, The Netherlands) and at the Human Nutrition Research Unit at Wageningen University and Research (Wageningen, The Netherlands). All study measurements will be performed according to strict standard operating procedures. The duration the study visits range from one to three hours. The study will be conducted in accordance with the Declaration of Helsinki and has been approved by the medical ethics committee Oost-Nederland (METC-Oost; NL82788.091.22). The trial is registered at clinicaltrials.gov (NCT05809466) and the SPIRIT 2013 checklist related to the manuscript can be found in supplementary Table 1.

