#### Randomization

Following inclusion, participants will be randomized to one of the three study arms on a 1:1:1 ratio, using block randomization with variable block sizes of 3, 6 and 9 to ensure equal allocation to each group. Randomization will be stratified for gender and partners will be randomized together. The randomization will be performed in Castor EDC by a member of the research team [31]. Considering the logistics of the study procedures, both the members of the research team and the participants will be aware of the group allocation.

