### Intervention

#### Study diets

All participants will attend monthly nutrition information meetings, commencing in the week prior to the initiation of the study diets. The content presented during these meetings will be based on the Dutch national dietary guidelines [32]. The participants assigned to the VEG and VEG-RE groups will be instructed to abstain from consuming any animal-based food products throughout the intervention period. During the nutrition information meetings, these groups will be informed regarding suitable plant-based replacements for animal-based food products, such as legumes, nuts, and dairy alternatives. Furthermore, these participants will receive guidance regarding the adoption of a vegan diet and will be given the opportunity to address any inquiries or concerns pertaining to the intervention. During these meetings, additional emphasis will be laid on the nutrients protein, cobalamin, vitamin D and calcium. The participants will be equipped with practical resources, including recipes and pocket-size hand-outs containing information regarding, for example, (non)vegan ingredients and vegan product logos.

With respect to the participants assigned to the control (OMNI) group, their habitual dietary intake as omnivores will form the basis for their dietary consumption throughout the intervention period. To address the possibility of potential confounding effects arising solely from increased adherence to the Dutch national dietary guidelines within the vegan groups, the control group will also participate in monthly nutrition information meetings. During these sessions, information about the Dutch national dietary guidelines [32] will be disseminated, including the recommendations regarding the consumption of animal-based food products. The control group will, however, not be strictly instructed to comply with these guidelines.

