#### Gastrointestinal health

Faecal samples and two aliquots of blood plasma will be collected at baseline and after 12 weeks from participants assigned to the VEG and OMNI groups. Faecal samples will be collected by the participants at home using a sterilized paper faecal bag. Subsequently, the samples are placed in sealed insulated containers by the participants, sealed in biohazard bags and stored in the freezer of the participants until their subsequent visit. Participants will be instructed to collect the faecal samples within 24 h prior to their subsequent visit to the research unit. The microbial DNA will be isolated from the faeces samples using Qiagen AllPrep DNA/RNA Mini kit (Qiagen) in combination with mechanical lysis. Metagenomic sequencing reads mapped to the human genome or aligned to Illumina adapters will be identified and removed using KneadData. The metagenomics data will reveal the taxonomy and the function of specific genes. Furthermore, blood samples will be collected in EDTA containing tubes and centrifuged at 1000 g and 4 ˚C for 15 min to obtain two aliquots of plasma. Untargeted and targeted metabolomics will be performed using LC/GC-MS on both the plasma and faecal samples. Targeted metabolomics will monitor tryptophan, tyrosine and branched-chain amino acid pathways, and oxidized amino acids. By contrast, untargeted metabolomics will explore unknown metabolic pathways and gut microbial metabolites to correlate gut microbiota functionality and circulating metabolites. By combining metagenomics with metabolomics data, and bioBakery workflow (KneadData, HUManN, MetaPhlAn, StrainPhlAN), we will investigate microbial communities using standardized and validated tools. The fusion of metagenomics and metabolomics data using Mmvec, MIMOSA2, and lineal models will link metabolites with microorganisms at strain/species level and functions.

The gastro-intestinal symptom rating scale (GSRS) questionnaire will be filled out by all participants at baseline and at the end of the intervention to assess the effect of the intervention on gastro-intestinal symptoms [41, 42]. The questionnaire includes 15 questions covering 5 common symptom clusters on a 7-point likert scale and takes approximately 3 to 5 min to fill out. These clusters are abdominal pain, reflux, indigestion, constipation and diarrhoea. Using this questionnaire, the participants will rate their symptoms over the past week.

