### Statistical analysis plan

All data will be treated according to the General Data Protection Regulation Act (EU GDPR) and will be collected using Castor EDC [31]. Analyses will be performed in R version 4.1.0. Prior to the analysis, group allocation will be blinded to the members of the research team that will perform the statistical analysis. Descriptive statistics will be used to explore and present baseline characteristics of the study population. Continuous data will be presented quantitatively as means and their 95% confidence intervals or, when not normally distributed, as median [interquartile range]. Categorical data will be presented as counts and percentages. Data will be analysed according to the intention-to-treat principle.

Independent samples t-tests will be performed to analyse the difference in change of thigh muscle volume and the difference in mixed MPS between groups VEG and OMNI and between groups VEG and VEG-RE. Data will be checked for normality using QQ-plots. Missing data may be imputed via multiple imputation or the related data may be eliminated. In case of a non-normal distribution, non-parametric tests will be used or data will be log-transformed. Furthermore, linear mixed models will be used to assess the differences between these groups for the other outcome measures. Participants will be added to the model as random factors. Treatment and timepoint will be added as fixed factors as main effects and their interaction. A maximum of three potential confounding factors may be added to each model as fixed factor. Model assumptions will be checked using QQ-plots and scatterplots. A two-sided p-value < 0.05 will be considered statistically significant. The Benjamini-Hochberg correction will be applied to adjust for multiple testing. In case more than two time points are tested and a significant treatment*time interaction is observed, a post-hoc analysis for will be performed using a Bonferroni correction.

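### The replacement rule is tied to diet start rather than to randomisation, so participants who know their arm can leave and drop out of both primary contrasts

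*Protocol article*

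**What the plan says.** The replacement rule stands in the Discussion, among the challenges and limitations: "participants that withdraw before the initiation of the intervention diets will be replaced". The sentence after it says that dropouts will be invited back for measurement so that an intention-to-treat analysis is possible. It does not say whether people who left before the diets count as dropouts.

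The Statistical analysis plan section states: "Data will be analysed according to the intention-to-treat principle". It also allows missing values to be handled either by multiple imputation or by removing the affected data, without choosing between them.

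On timing, the Randomization section says: "Following inclusion, participants will be randomized to one of the three study arms on a 1:1:1 ratio". It adds that "both the members of the research team and the participants will be aware of the group allocation". Under Study diets, the nutrition meetings are described as "commencing in the week prior to the initiation of the study diets", and their content differs between the vegan arms and the control arm. Under Gastrointestinal health, stool and plasma samples "will be collected at baseline and after 12 weeks from participants assigned to the VEG and OMNI groups".

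**The concern.** An intention-to-treat comparison rests on everyone randomised, in the arm to which they were randomised. A rule that replaces people up to the start of the diets, when allocation is already open, creates a window in which someone can learn the arm, leave, and be succeeded by someone else. If the person who left is then not analysed, the comparison depends partly on who was willing to stay in each arm.

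Withdrawal in that window could plausibly depend on the arm. One arm continues its usual diet, one changes to a vegan diet, and one does that and trains twice a week. The Discussion itself calls the change to a vegan diet complex. It also says that volunteers may be drawn by an interest in plant-based eating, so allocation to the control arm could disappoint some of them. The direction is therefore uncertain. The VEG arm appears in both primary contrasts, so selection there would affect both. Selection in OMNI or VEG-RE would affect one.

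**Working it through.** **Step 1: does the replacement window extend beyond allocation?**

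- Randomisation follows inclusion, and participants and team know the arm (Randomization).
- Baseline stool sampling is confined to VEG and OMNI (Gastrointestinal health; Table 2 footnote). The arm must therefore be known before that sampling.
- The first nutrition meeting, with arm-specific content, falls in the week before the diets (Study diets).
- The first deuterated-water day is one day before the diets (Deuterated water protocol).
- "The study duration for enrolled participants will be approximately 14 weeks". Set against a 12-week intervention, 14 − 12 = 2 weeks lie outside it, which is consistent with a pre-diet period.

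The window for replacement closes at diet start, so it includes a period after open allocation. It may also include withdrawals between inclusion and randomisation, where replacement does no harm.

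**Step 2: does any text keep replaced participants in the analysis?** The Discussion and the Statistical analysis plan section are the only places that bear on this. Neither says that a replaced participant stays in the set, is reported by arm or is followed up. Neither says how the replacement is allocated. The option to remove missing data would allow such participants to be left out.

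**Step 3: how large could the effect be?** The article gives no expected number of pre-diet withdrawals and no outcome difference for them, so there is no stated figure to reproduce. The calculation below is an illustration.

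Inputs from the Sample size calculation section: 24 recruited per arm and a planned effect of 4 percentage points. Assumed: k pre-diet withdrawals in one arm, each replaced so that 24 remain, and D, the difference in mean 12-week change between stayers and leavers, had the leavers been measured. Replacements are assumed to respond like stayers.

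- Randomised to the arm: 24 + k
- Share lost: f = k / (24 + k)
- Mean of all randomised = (24 × stayer mean + k × leaver mean) / (24 + k), so the analysed mean is off by f × D

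| k | Randomised | f | D = 1 | D = 2 | D = 4 |
|---|---|---|---|---|---|
| 1 | 25 | 4.0% | 0.04 | 0.08 | 0.16 |
| 2 | 26 | 7.7% | 0.08 | 0.15 | 0.31 |
| 3 | 27 | 11.1% | 0.11 | 0.22 | 0.44 |
| 5 | 29 | 17.2% | 0.17 | 0.34 | 0.69 |

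Relative to the planned 4 points, the range runs from 0.04/4 = 1% to 0.69/4 = 17%.

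The bias in a contrast is the difference between the two arms' shifts. The table gives that bias only if the comparator has none. Equal shifts in the same direction would cancel.

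**Step 4: what does replacement itself contribute?** Without replacement, an analysis of completers would be off by (k/24) × D. That is 1/24 × 1 = 0.04 points at the low end and 5/24 × 4 = 0.83 at the high end. The shift is of the same order either way. It comes from selective withdrawal with an unobserved outcome. Replacement brings n back to 24 and leaves the selection in place.

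**The case against.** The strongest reply is that replacement governs enrolment and intention-to-treat governs analysis. If replaced participants stay in the set with missing outcomes and the randomised total rises above 72, both rules hold. That is correct. A reader might infer that the two rules cannot both be followed, but the document does not support this: it nowhere says that replaced participants leave the analysis. What stands is that it nowhere keeps them in either, and it permits removal of missing data.

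A reader might also infer that a replacement inherits the vacated arm, so that the arm fills with people who accept it. No text says so. The only mechanism described is stratified block randomisation.

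A third reply is that an article leaves analysis-set definitions to the full protocol. That is fair for an omission. Here, however, the article states an affirmative rule and ties it to diet start.

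Two further points limit the concern. Differential refusal is plausible but not shown: biopsies, deuterated water and MRI fall on all arms, and procedures are explained before consent. And someone who leaves before the baseline MRI has no computable change even if a week-12 scan is obtained, so follow-up cannot recover every such case.

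**Conclusion.** The concern holds as an unreconciled rule. As written, the article allows randomised participants who know their arm to be replaced, and it does not secure their place in the intention-to-treat analysis. Arm-dependent withdrawals can therefore be left out of both primary contrasts without any departure from the text.

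The size is a risk, not an estimate. With 1 to 5 withdrawals in one arm, D between 1 and 4 points and no shift in the comparator, the arm mean moves by about 0.04 to 0.7 points against the planned 4. That is modest unless withdrawals are many and strongly selective. A reader might reach a larger share by letting leavers differ by a full standard deviation of change, 5 points. The document gives no ground for that, and it would exceed the whole planned effect.

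**What to change.** Adopt one of two wordings.

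1. Limit replacement to participants who withdraw before randomisation.
2. If replacement up to diet start is kept, state that:
   - all randomised participants remain in the intention-to-treat set in their allocated arm;
   - withdrawals between randomisation and diet start are reported by arm;
   - these participants are offered the same follow-up as other dropouts;
   - their missing outcomes are handled by multiple imputation rather than elimination;
   - any added participant takes the next allocation on the randomisation list.

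The cost is a few sentences and a few more participants with missing outcomes in the primary set. Under the second wording the randomised total may exceed 72. Imputation corrects the selection only as far as the recorded variables explain who left, and least for those without a baseline scan. Reporting by arm matters for that reason, because it lets readers judge what remains.
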